## 9. Participant Timeline

The participant timeline is described in **Figure 4**.

|                  | STUDY PERIOD                   |            |                                                                                      |   |   |   |   |   |   |   |           |    |    |
|------------------|--------------------------------|------------|--------------------------------------------------------------------------------------|---|---|---|---|---|---|---|-----------|----|----|
|                  | Enrolment                      | Allocation | Treatment phase                                                                      |   |   |   |   |   |   |   | Follow-up |    |    |
| Timepoint (week) | −1                             | 0          | 1                                                                                    | 2 | 3 | 4 | 5 | 6 | 7 | 8 | 12        | 16 | 20 |
| ENROLLMENT:      | ×                              |            |                                                                                      |   |   |   |   |   |   |   |           |    |    |
|                  | ×                              |            |                                                                                      |   |   |   |   |   |   |   |           |    |    |
|                  | ×                              |            |                                                                                      |   |   |   |   |   |   |   |           |    |    |
|                  |                                | ×          |                                                                                      |   |   |   |   |   |   |   |           |    |    |
| INTERVENTIONS:   |                                |            |                                                                                      |   |   |   |   |   |   |   |           |    |    |
|                  |                                |            | [figure not shown]   |   |   |   |   |   |   |   |           |    |    |
|                  |                                |            | [figure not shown] |   |   |   |   |   |   |   |           |    |    |
| ASSESSMENTS:     |                                |            |                                                                                      |   |   |   |   |   |   |   |           |    |    |
|                  | Daily Consumption of Methadone | ×          |                                                                                      | × |   | × |   | × |   | × | ×         | ×  | ×  |
|                  | opioid craving VAS             | ×          |                                                                                      | × |   | × |   | × |   | × | ×         | ×  | ×  |
|                  | COWS                           | ×          |                                                                                      | × |   | × |   | × |   | × | ×         | ×  | ×  |
|                  | BAI                            | ×          |                                                                                      |   |   | × |   |   |   | × | ×         | ×  | ×  |
|                  | BDI-II                         | ×          |                                                                                      |   |   | × |   |   |   | × | ×         | ×  | ×  |
|                  | PSQI                           | ×          |                                                                                      |   |   | × |   |   |   | × | ×         | ×  | ×  |
|                  | ADVERSE EVENTS:                |            |                                                                                      | × | × | × | × | × | × | × | ×         | ×  | ×  |

Figure 4: Schedule of enrolment, interventions, and assessments

## 10. Sample Size Calculation

Estimates of clinically meaningful differences between the manual acupuncture group and the sham control group are based on the data of Nosyk et al. and our previous study [18,19,34]. We assume an efficacy rate of 70% for the manual acupuncture

group and 36% for the sham control group, 42 participants per group are needed at 5% significance with 90% power. This provided exceeding 99% power to detect a mean difference of 10 (SD 8) in opioid craving VAS scores between the two groups at a 5% significance level for a 2-sided test (required 25 participants per group). Thus, anticipating approximately 15% attrition, at least 50 participants per group (n = 100 in total) are required.

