To investigate the relationship between daily consumption of methadone and the intensity of opioid craving over a 20-week period, scatter plots are employed as a visual representation in this study with the x-axis representing the opioid craving VAS and the y-axis representing the daily consumption of methadone. The resulting scatter plot allows for the examination of the correlation between these two variables, providing insights into the potential influence of methadone intake on opioid craving levels over time.

Efficacy analyses will be performed for both the full analysis set (FAS) population and the per-protocol set (PPs) population. The FAS population will consist of all randomized patients who received at least one treatment. In a PPs analysis, only patients who complete all the clinical trials according to the protocol are counted towards the results. Besides, the PPs population in our research will meet these criteria: the experimental treatment requirements; the main variables can be determined; no missing baseline variables; no major violation of the test scheme. Safety analyses will be performed on the safety population, which will be comprised of all randomized subjects who have been administered at least one treatment. A PP analysis is carried out as a sensitivity analysis compared with the results obtained using the FAS analysis. When the PPs and FAS analysis conclusions are not the same, it is necessary to analyze the possible reasons and discuss them.

Primary outcomes used 2-sided tests at the 2.5% significance level. All other statistical tests are 2-sided at the 5% significance level.

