## **6. Statistical Considerations**

### **6.1 Study Hypothesis**

The primary study hypothesis is that manual acupuncture is more efficacy than sham acupuncture in reducing methadone dose and opioids craving in MMT clients.

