### **7.4 Analyses for Outcomes**

The analysis of proportion of participants with at least 20% reduction from baseline in the amount of methadone dose is performed using a generalized linear mixed model. For opioid craving VAS and all secondary outcomes, analysis is conducted utilizing a

linear mixed-model. For above models, values measured at baseline are used as covariates; intervention assignment, visit and intervention  $\times$  visit interaction are as fixed effects; and treatment centre and centre  $\times$  intervention interaction are as random effects. Before building the final model, we assess the poolability of treatment effects across centres by including centre  $\times$  intervention interaction in the model. If *P*-values corresponding to the interaction term for both primary endpoints are greater than 0.10, the treatment effect is homogenous across centres and centre  $\times$  intervention interaction will not be included in the final model. Primary outcomes use 2-sided tests at the 2.5% significance level. All other statistical tests are 2-sided at the 5% significance level. Dynamic data on the reduction in the methadone consumption and the opioid craving VAS score will be demonstrated in the figures, separated by two groups. Each row in the figures represents the reduction dose of the daily consumption of methadone (the opioid craving VAS score) for one participant. To investigate the relationship between daily consumption of methadone and the intensity of opioid craving over a 20-week period, scatter plots will be employed as a visual representation in this study with the x-axis representing the opioid craving VAS and the y-axis representing the methadone dose. The resulting scatter plot allows for the examination of the correlation between these two variables, providing insights into the potential influence of methadone intake on opioid craving levels over time.

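### The sample size is calculated at 5% significance but both primary outcomes are tested at 2.5%, so power for the dose outcome is about 82-86%, not 90%

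*Combined protocol and SAP*

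**What the plan says.** Protocol section 10 sizes the trial on the dose outcome, the proportion of participants whose methadone dose falls by at least 20% after 8 weeks. The assumed rates are given as "We assume an efficacy rate of 70% for the manual acupuncture" group and "36% for the sham control group", and the result is that "42 participants per group are needed at 5% significance with 90% power". The same paragraph claims "exceeding 99% power to detect a mean difference of 10 (SD 8) in opioid craving VAS scores", again "at a 5% significance level for a 2-sided test (required 25 participants per group". Allowing for 15% attrition, it arrives at 50 per group.

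The analysis sections use a different level. Protocol section 11 says "Primary outcomes used 2-sided tests at the 2.5% significance level", and SAP section 7.4 repeats it: "Primary outcomes use 2-sided tests at the 2.5% significance level". Nothing in either document carries the 2.5% back into section 10 or explains the difference.

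SAP section 6.1 states the hypothesis as "manual acupuncture is more efficacy than sham acupuncture in reducing methadone dose and opioids craving in MMT clients". No section says whether success on one primary outcome is enough or whether both are needed.

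**The concern.** Testing two primary outcomes at 2.5% each is a Bonferroni split of 5%. It is a valid way to control familywise error when either outcome can carry the trial, but it makes each test harder to pass, and the sample size has to reflect that. Here it does not.

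The dose outcome limits the trial: it needs 42 per group, against 25 for craving. It therefore bears nearly the whole cost. Craving has far more power than it needs, and under a fixed split its share of alpha is never passed to the dose outcome, even after craving has succeeded.

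At stake is a core planning figure that ethics committees, editors and readers rely on, together with avoidable power on the outcome that needs it most. Type I error and the effect estimate are not affected.

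**Working it through.** **Inputs.** From protocol section 10: p1 = 0.70, p2 = 0.36, 42 evaluable per group, 15% attrition; craving difference 10, SD 8. Allocation is 1:1 (protocol section 3.1). The analysis level is two-sided 2.5% (protocol section 11, SAP section 7.4). Section 10 does not state sidedness for the dose outcome. Two-sided is assumed, because the craving sentence says so and it agrees with the stated 42.

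Derived quantities: difference d = 0.34; mean proportion p = 0.53; V = 0.70×0.30 + 0.36×0.64 = 0.4404; V0 = 2×0.53×0.47 = 0.4982. Critical values: z = 1.960 at 5%, 2.241 at 2.5%; 1.2816 for 90% power.

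**Step 1: check the plan's figure at 5%.**
- Pooled: n = (1.960√0.4982 + 1.2816√0.4404)² / 0.34² = 43.2.
- Unpooled: n = (1.960 + 1.2816)² × 0.4404 / 0.34² = 40.0.

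The stated 42 lies between the two, and 42/0.85 = 49.4 rounds up to the stated 50.

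**Step 2: power with 42 per group.**
- Pooled: Φ[(d√n − z√V0)/√V], with d√n = 0.34×√42 = 2.203.
- Unpooled: Φ[d√n/√V − z].
- Exact: binomial probabilities summed over all tables that the uncorrected chi-square test rejects.

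| Method | 5% | 2.5% |
|---|---|---|
| Pooled z | Φ(1.236) = 89.2% | Φ(0.936) = 82.5% |
| Unpooled z | Φ(1.360) = 91.3% | Φ(1.079) = 86.0% |
| Exact power of chi-square | 90.9% | 81.6% |

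Fisher's exact test would give 75.2% at 2.5%. At 5% it gives only 86.6%, so it is not the basis of the stated 90%.

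**Step 3: size needed for 90% power at 2.5%.**
- Pooled: 51.2, so 52 per group; 52/0.85 = 61.2, so 62 randomised.
- Unpooled: 47.3, so 48 per group; 48/0.85 = 56.5, so 57 randomised.

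That is 114-124 in total against the planned 100.

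**Step 4: craving at 2.5%.** With 42 per group the noncentrality is 10/(8√(2/42)) = 5.73, and the t-test has 99.97% power.

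**Step 5: dose power under Holm.** The dose outcome is declared positive if its P-value is at most 2.5%, or at most 5% when craving has passed 2.5%. Let q be the power of craving at 2.5%, and treat the two tests as independent. Dose power is then (1 − q)×(power at 2.5%) + q×(power at 5%).

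| Craving assumption | q | Dose power (pooled to unpooled) |
|---|---|---|
| Difference 10, SD 8 (the plan) | 0.9997 | 89.2-91.3% |
| Difference 4 (the MCID in protocol section 6.1.2), SD 8 | 0.51 | 85.9-88.7% |

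**The case against.** Four points can be made for the plan.

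**More than 42 per group may inform the test.** The trial randomises at least 50 per group, the full analysis set keeps most of them, missing values are imputed, and dose comes from daily clinic records that may exist for people who stop acupuncture. If all 50 gave full information, power at 2.5% would be 89.2% (pooled), 91.6% (unpooled) or 88.2% (exact chi-square). This stands as an upper bound. But section 10 ties its 90% to 42, and adds participants because it expects to lose information from dropouts. Imputation under missing at random does not restore that information.

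**Section 10 is correct at the level it names.** True: at 5% the figure is sound. The error is that this is not the level at which the outcome will be tested.

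**The success rule is open.** If SAP section 6.1 means that both outcomes are required, no split is needed, the 5% in section 10 is right, and the 2.5% statements are what must change. This stands. It alters which sentence to correct, but the two sections still disagree.

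**A fixed split is legitimate, and Holm's gain depends on craving.** Both are true. Holm never rejects less than the fixed split, but the full return to 89-91% depends on the plan's craving assumption. With a true difference of only 4 points, recovery is partial.

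In addition, the planned analysis is a generalized linear mixed model, so two-proportion power is an approximation. It is evidently the one section 10 itself uses.

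**Conclusion.** The concern holds. As the plan is written, power for the dose outcome at its actual two-sided 2.5% level is about 82-86%, a loss of about 5-9 points from the same method's figure at 5%. The risk of missing the assumed 70% versus 36% difference is about 14-18% instead of 10%.

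This rests on 42 evaluable participants per group, a two-sided test and a simple comparison of two proportions. It would shrink towards nothing only if nearly all 50 randomised per group contributed full information. Craving is essentially unaffected.

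**What to change.** 1. State the success rule in SAP section 6.1: a positive trial on either primary outcome, or only on both.
2. If either suffices, replace the fixed split in protocol section 11 and SAP section 7.4 with the Holm procedure: compare the smaller of the two primary P-values with 2.5% and, if it passes, the other with 5%. Familywise error stays at 5% whatever the correlation between the outcomes.
3. If both are required, test each at 5% and delete the 2.5% statements. Section 10 then uses the right level.
4. Restate section 10 to match. Under the either-outcome rule, give about 82-86% for the dose outcome at 2.5% alone and about 90% under Holm, noting that the latter relies on the assumed craving difference of 10 with SD 8.

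The cost is a sentence or two on the testing rule and a restated power figure. No patients are added. The change should be fixed before unblinding, because adopting Holm afterwards would look data-driven.

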## 11. Statistical Analysis

Statistical analysis will be performed by the Clinical Research and Big Data Laboratory, South China Research Center for Acupuncture and Moxibustion, Guangzhou University of Chinese Medicine. The statistician will be blinded to group allocation until final unblinding. SAS 9.4 will be utilized for data analysis. Missing data are filled by using multiple imputation.

Continuous variables are reported as the mean with standard deviation or median and interquartile range. Categorical variables are described as numbers and percentages using  $\chi^2$  test or Fisher's exact test. Longitudinal measures through 20 weeks (8 weeks of intervention and 12 weeks of follow-up) are analyzed for all outcomes. The analysis of proportion of participants with at least 20% reduction from baseline in the amount of methadone dose is performed using a generalized linear mixed-model. For opioid craving VAS and all secondary outcomes, analysis is conducted utilizing a linear mixed-model. For above models, values measured at baseline are used as covariates; intervention assignment, visit and intervention  $\times$  visit interaction are as fixed effects; and treatment centre and centre  $\times$  intervention interaction are as random effects. We assessed the poolability of treatment effects across centres by including centre  $\times$  intervention interaction in the model. If *P*-values corresponding to the centre  $\times$  intervention interaction term for both primary endpoints are greater than 0.10, the treatment effect is homogenous across centres [59].

Dynamic data will be demonstrated on the reduction in the methadone consumption and the opioid craving VAS score in the figures, separated by the manual acupuncture and sham group. Each row in the figures represents the reduction dose of

the daily consumption of methadone (the opioid craving VAS score) for one participant. Individuals who discontinue participation early appear at the bottom of each plot, whereas those with complete data appear at the top.

To investigate the relationship between daily consumption of methadone and the intensity of opioid craving over a 20-week period, scatter plots are employed as a visual representation in this study with the x-axis representing the opioid craving VAS and the y-axis representing the daily consumption of methadone. The resulting scatter plot allows for the examination of the correlation between these two variables, providing insights into the potential influence of methadone intake on opioid craving levels over time.

Efficacy analyses will be performed for both the full analysis set (FAS) population and the per-protocol set (PPs) population. The FAS population will consist of all randomized patients who received at least one treatment. In a PPs analysis, only patients who complete all the clinical trials according to the protocol are counted towards the results. Besides, the PPs population in our research will meet these criteria: the experimental treatment requirements; the main variables can be determined; no missing baseline variables; no major violation of the test scheme. Safety analyses will be performed on the safety population, which will be comprised of all randomized subjects who have been administered at least one treatment. A PP analysis is carried out as a sensitivity analysis compared with the results obtained using the FAS analysis. When the PPs and FAS analysis conclusions are not the same, it is necessary to analyze the possible reasons and discuss them.

Primary outcomes used 2-sided tests at the 2.5% significance level. All other statistical tests are 2-sided at the 5% significance level.

## **12. Research Ethics Approval and Consent or Assent**

The trial is designed in accordance with the principles of the Declaration of Helsinki. The trial protocol (version number: 3.0, version date: February 20, 2022) has been approved by the Ethics Committee of the Panyu Hospital of Traditional Chinese Medicine (Ethics approval numbers: 2022029) on February 22, 2022. Written

informed consent will be obtained from each participant before they enter the trial.

### **13. Quality Control, Data Management and Monitoring**

Before recruitment, the entire team will be required to attend a training workshop, which ensures strictly comply with the study protocol and totally understanding of the trial administration process. The interventions will be performed by licensed acupuncturists with more than three years of experience in hospitals or clinics. They are also received a brochure about the protocol and standard operation procedure for acupuncture.

The data will be carefully collected and recorded on CRFs. All data will be put onto the computer with password protection by staff blinded to group allocation and checked twice by investigators after data entry. Data quality will be checked regularly by research assistants and supervised by monitors. The original CRFs and all other forms will be archived securely at the Medical College of Acu-Moxi and Rehabilitation of Guangzhou University of Chinese Medicine. Confidentiality is ensured by storing data in a password-protected database, for which only the research team has the password. Paper-based record forms are identified by numbers and stored in a locked cupboard. Any published patient data are not allowed personal identification, only group data could be published.

### **14. Dissemination Policy**

The results of this trial are expected to be published in peer-reviewed journals and presented at national and international meetings.

### **Abbreviations**

AEs: Adverse events; BAI: Beck Anxiety Inventory; BDI- II: Beck Depression Inventory II; FAS: Full analysis set; JTN: Jin's three-needle acupuncture; MCID: Minimal clinically important difference; MMT: Methadone maintenance therapy, OUD: Opioid Use Disorder; PPs: Per-protocol set; PSQI: Pittsburgh Sleep Quality

Index; RCT: Randomized controlled trial; VAS: Visual analogue scale; WHO: World Health Organization.

## Appendix 1: Diagnostic criteria for opioid use disorder (DSM-5)

### Diagnostic Criteria for Opioid Use Disorder

A problematic pattern of opioid use leading to clinically significant impairment or distress, as manifested by at least two of the following, occurring within a 12-month period:

1. Opioids are often taken in larger amounts or over a longer period than was intended.
2. There is a persistent desire or unsuccessful efforts to cut down or control opioid use.
3. A great deal of time is spent in activities necessary to obtain the opioid, use the opioid, or recover from its effects.
4. Craving, or a strong desire or urge to use opioids.
5. Recurrent opioid use resulting in a failure to fulfill major role obligations at work, school, or home.
6. Continued opioid use despite having persistent or recurrent social or interpersonal problems caused or exacerbated by the effects of opioids.
7. Important social, occupational, or recreational activities are given up or reduced because of opioid use.
8. Recurrent opioid use in situations in which it is physically hazardous.
9. Continued opioid use despite knowledge of having a persistent or recurrent physical or psychological problem that is likely to have been caused or exacerbated by the substance.
10. Tolerance, as defined by either of the following:
  - a. A need for markedly increased amounts of opioids to achieve intoxication or desired effect.
  - b. A markedly diminished effect with continued use of the same amount of an opioid.
11. Withdrawal, as manifested by either of the following:
  - a. The characteristic opioid withdrawal syndrome (refer to Criteria A and B of the criteria set for opioid withdrawal, pp. 547-548).
  - b. Opioids (or a closely related substance) are taken to relieve or avoid withdrawal symptoms.

**Note:** This criterion is not considered to be met for those individuals taking opioids solely under appropriate medical supervision.

